### Exposure

The exposure of interest is an UTI. The risk period is 0–90 days following an UTI. This period was chosen as previous research has shown an increase in acute MI and stroke risk in the 1–90 days following an UTI.^6^ There will be a prerisk period of 7 days before the risk period, to allow for the situation where an individual has an UTI for several days prior to consultation, so events in this period are not erroneously attributed to the baseline period. Individuals can be exposed to an UTI more than once during the observation period. Each exposure will be followed by the same 90-day risk period. Baseline periods are all other times.

To ascertain UTI, we developed definitions that reflected the Public Health Wales Microbiology Division’s standard operating procedure for the investigation of urine.^36^ These procedures are followed by NHS microbiology laboratories across Wales. For each definition, the data sources required and the clinical scenario represented is summarised in table 2, and the code lists used are given in online supplemental material B–D. In our primary analysis, an individual will be regarded as being exposed to an UTI if the following events occur within a 7-day window:

A General Practice (GP) record of an UTI diagnostic or symptom code.A GP record of an antibiotic prescription.A microbiology record of a urine sample with bacterial growth of a single organism of ≥1x10^8^ colony-forming units (CFU) per litre and white cell count (WCC)≥1x10^8^/L. If there are two organisms grown, both must demonstrate growth of ≥1x10^8^ CFU per litre. More than two organisms will be regarded as mixed growth and thus not supportive of an UTI diagnosis. In a sensitivity analysis, we will widen the microbiological criteria and include all urine samples with bacterial growth of a single organism of ≥1x10^7^ CFU per litre, irrespective of the WCC.

**Table 2 T2:** Definitions of UTI for primary and secondary analyses. As the UTI definitions are combinations of two or more components, the start of the risk period is defined as the date of the earliest component

	UTI-related read code in GP data (online supplemental material B)	Antibiotic prescription in GP data (online supplemental material C)	UTI-related ICD-10 code in PEDW (online supplemental material D)	Urine culture results in WRRS	Time frame	Clinical scenario

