Primary analysis	Yes	Yes	No	Yes, showing bacterial growth of ≥1x10^8^ CFU/L and WCC ≥1x10^8^ /L	Three codes occur within a 7-day window	GP clinically suspected and microbiologically confirmed UTI
Secondary analysis 1	Yes	Yes	No	Yes, showing mixed bacterial growth (any descriptor for ‘mixed growth’ or >3 organisms).	Three codes occur within a 7-day window	GP clinically suspected UTI with mixed growth
Secondary analysis 2	Yes	Yes	No	No	Same day	GP clinically diagnosed and treated UTI. It is important to consider this group as not all individuals with suspected UTI have urine culture, and limiting to those with culture is subject to selection bias.
Secondary analysis 3	Yes	Yes	No	Yes, showing bacterial growth of <1x10^7^ CFU/L.	Three codes occur within a 7- day window	UTI is clinically suspected but not supported by microbiology. This group is important to understand if early symptoms and signs of acute MI or stroke are attributed to UTI.
Secondary analysis 4	No	No	Yes	Yes, showing bacterial growth of ≥1x10^8^ CFU/L and WCC ≥1x10^8^ /L	Two codes occur within a 7-day window	UTI diagnosed and/or treated in hospital
Secondary analysis 5	Yes, OR ICD-10 code	Yes, OR ICD-10 code	Yes, OR: UTI Read code AND antibiotic Read code	Yes, showing bacterial growth of ≥1x10^8^ CFU/L and WCC ≥1x10^8^ /L	Two/three codes occur within a 7-day window	GP clinically suspected and microbiologically confirmed UTI or UTI diagnosed and/or treated in hospital

GP, General Practice; ICD-10, International Classification of Disease version 10; PEDW, Patient Episode Database for Wales; UTI, urinary tract infection; WCC, white cell count; WRRS, Welsh Results Reporting Service.

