In secondary analysis 1, we will estimate the risk of MI and stroke among individuals with a GP record of an UTI code and antibiotic prescription, and a microbiology record of a urine sample with mixed bacterial growth (any descriptor for ‘mixed growth’ or >3 organisms). This is an important analysis given the uncertain clinical significance of mixed bacterial growth in an individual with symptoms of UTI. In secondary analysis 2, an individual will be regarded as exposed to UTI with only a GP record of a diagnostic or symptom code and an antibiotic prescription (no microbiology). Secondary analysis 3 will estimate the risk of MI and stroke among individuals where UTI was suspected and treated by the GP, but urine microbiology showed bacterial growth of<1x10^7^ CFU per litre (not supportive of an UTI diagnosis). Secondary analysis 4 will focus on individuals with a hospital admission with an UTI-related ICD-10 code and a microbiology record of a urine sample with bacterial growth of a single organism of ≥1x10^8^ CFU per litre and white blood cells ≥1x10^8^ per litre. As for the primary analysis, if there are two organisms grown, both must demonstrate growth of ≥1x10^8^ CFU per litre, and more than two organisms will be regarded as mixed growth. Secondary analysis 5 combines the primary analysis, and secondary analysis 4, considering individuals with either a GP record of an UTI code and antibiotic prescription, or a hospital admission with an UTI-related ICD-10 code, and a microbiology record of a urine sample with bacterial growth of a single organism of ≥1x10^8^ CFU per litre and white blood cells ≥1x10^8^ per litre. In the primary analysis, any hospital diagnosed UTI is likely to count towards baseline time, whereas they would be included in exposed time here.

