### Sensitivity and subgroup analyses

We will perform several sensitivity and subgroup analyses to assess the robustness of the findings of our primary analysis to different assumptions:

We will explore the impact of using a wider definition of MI and stroke, including ICD-10 codes for acute coronary syndromes and transient ischaemic attacks. This will include events that have potentially been missed by our main definition and assess how sensitive our findings are to the definition of MI and stroke.We will explore the impact of widening the microbiological definition of UTI to bacterial growth of a single organism of ≥1x10^7^ CFU per litre irrespective of WCC.We will differentiate first-ever MI or stroke from recurrent events, and report risk estimates separately. This analysis will exclude individuals with a PEDW record of an event before the observation period, and include only those who have their first ever event during the observation period.We will extend the prerisk period to 14 days. Some individuals may have had an UTI for several days prior to diagnosis, and so an acute MI or stroke during this time may relate to exposure but without a prerisk period, would count towards the baseline period.We will repeat the analysis excluding individuals who died within 30 days of an event to examine the potential effect of an event dependent observation period.We will restrict the definition of UTI to include only antibiotic prescriptions for nitrofurantoin (currently recommended first-line therapy) to explore whether the choice of antibiotic impacts the findings.We will use interaction terms to assess the impact of specific bacterial organisms on the relationship between UTI and MI or stroke.We will examine whether the COVID-19 pandemic may affect our findings by (1) excluding individuals whose MI or stroke occurred in 2020, and (2) including an interaction term to explore whether the association between exposure and outcome differs in 2020 vs pre-2020.We will include an interaction term to explore whether the association between exposure and outcome differs in those with and without a history of diabetes, given its potential role as a risk factor of both UTI and MI/stroke.

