### Sample size and power

Our initial work has identified 51 656 individuals with acute MI and 58 146 with stroke in the SAIL Databank who meet all inclusion criteria. In the previous study by Smeeth *et al*,^6^ the sample size was 53 709 for acute MI, and 55 157 for stroke, where 16% of acute MI cases, and 21% of stroke cases were exposed to UTI.^6^ Based on a conservative exposure rate of 10%, and an at-risk window of 90 days, we estimated the effect size that could be reliably detected with our potential sample size, using the sample size function in the SCCS package in R. The available sample provides 90% power to detect an IRR of 1.3 at the alpha=0.05 level, which is smaller than the IRRs detected in Smeeth *et al*^6^

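### Secondary analysis 3 rules out UTI on culture growth alone, so its check for misattributed MI or stroke symptoms may be blurred by episodes with a raised white cell count

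*Protocol article*

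**What the plan says.** In the Exposure section of the protocol article, the primary definition combines a GP code, an antibiotic prescription and a supporting urine result within 7 days. The urine criterion is "A microbiology record of a urine sample with bacterial growth of a single organism of ≥1x10^8^ colony-forming units (CFU) per litre and white cell count" of at least 1x10^8/L. Table 2 applies the same pair of cut-offs to secondary analyses 4 and 5.

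Secondary analysis 3 keeps the GP code and the prescription but changes the urine criterion to "Yes, showing bacterial growth of <1x10^7^ CFU/L". The text after Table 2 agrees: "urine microbiology showed bacterial growth of<1x10^7^ CFU per litre (not supportive of an UTI diagnosis"). Neither place adds a WCC condition. Table 2 gives the purpose of the group: "This group is important to understand if early symptoms and signs of acute MI or stroke are attributed to UTI".

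One item under Sensitivity and subgroup analyses varies the microbiological cut-offs, by "widening the microbiological definition of UTI to bacterial growth of a single organism of ≥1x10^7^ CFU per litre irrespective of WCC".

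On the source of the thresholds, the authors write that "we developed definitions that reflected the Public Health Wales Microbiology Division’s standard operating procedure for the investigation of urine". That procedure is not part of the document.

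**The concern.** The Introduction criticises the one earlier study of UTI and cardiovascular events because clinical codes alone could not separate true UTI from non-specific symptoms that were the first signs of an event. Secondary analysis 3 is the part of the plan that addresses this directly, and it also serves the second objective. For that purpose the group should contain as few true UTIs as the data allow.

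The plan uses WCC when it confirms a UTI but not when it declares one unsupported. A patient with urinary symptoms, an antibiotic, low growth and a WCC above the plan's own cut-off is counted as unsupported. The Introduction names the inflammatory response to infection as a route to cardiovascular events, so such an episode could plausibly carry part of the effect under study.

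An excess of events in this group then has two explanations. If early MI or stroke symptoms were recorded as UTI, the causal reading of the primary result is weakened. If low-count infection or inflammation is present, it is not. The plan as written gives no direct way to separate them.

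**Working it through.** **1. Definitions side by side.** Take episodes with a GP code, an antibiotic and single-organism growth or low growth, all within 7 days. The cut-offs come from Exposure, Table 2, and Sensitivity and subgroup analyses.

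| Growth (CFU/L) | WCC ≥1x10^8/L | WCC <1x10^8/L |
|---|---|---|
| ≥1x10^8 | Primary; widened sensitivity | Widened sensitivity |
| 1x10^7 to <1x10^8 | Widened sensitivity | Widened sensitivity |
| <1x10^7 | **Secondary 3** | Secondary 3 |

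The bold cell is the one at issue: it meets the primary definition's white-cell criterion but sits in the unsupported group. Episodes in any cell might also enter secondary analysis 2 if its entry for culture means not required and the same-day rule is met.

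**2. The plan's own effect size.** The article states "The available sample provides 90% power to detect an IRR of 1.3 at the alpha=0.05 level", "Based on a conservative exposure rate of 10%, and an at-risk window of 90 days". The point does not depend on this figure, but 1.3 is the only design IRR in the document, so I checked it before using it. I used the signed-root likelihood-ratio formula for self-controlled case series without age effects, two-sided (the article does not state sidedness):

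- r = 90 / observation days
- π = IRR·r / (IRR·r + 1 − r)
- A = 2[π·ln(IRR) − ln(IRR·r + 1 − r)]
- B = ln(IRR)²·π(1 − π) / A
- exposed cases needed = (z for α/2 + z for power × √B)² / A

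Observation times are the means under Summary of cases.

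| | MI | Stroke |
|---|---|---|
| Mean observation (days) | 2981 to 3251 | 2796 to 2981 |
| Exposed cases needed | 4,564 to 4,961 | 4,292 to 4,564 |
| Available (10% of 51 656; 58 146) | about 5,166 | about 5,815 |
| Power at IRR 1.3 | 91% to 93% | 95% to 96% |

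The stated power is reproduced. The 1.3 is a detectable effect, not an expected one.

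**3. Size of the blurring.** Let p be the share of secondary analysis 3 episodes with WCC ≥1x10^8/L. Suppose these carry the full UTI effect, all other episodes carry none, and baseline event rates are equal in the two parts. The average rate multiplier in the risk window is then

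p × IRR + (1 − p) × 1 = 1 + p × (IRR − 1).

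| p (assumed) | True IRR 1.3 | True IRR 2.0 (assumed) |
|---|---|---|
| 10% | 1 + 0.10 × 0.3 = 1.03 | 1 + 0.10 × 1.0 = 1.1 |
| 20% | 1 + 0.20 × 0.3 = 1.06 | 1 + 0.20 × 1.0 = 1.2 |
| 30% | 1 + 0.30 × 0.3 = 1.09 | 1 + 0.30 × 1.0 = 1.3 |

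These values arise with no misattribution of symptoms at all. If only some raised-WCC episodes carry the effect, the shift is proportionally smaller.

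**The case against.** The case for leaving the plan as it is has several sound parts.

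- **There is no contradiction.** Table 2 and the text define secondary analysis 3 identically, and its limit meets the widened rule at 1x10^7 CFU/L without overlap. A reader might infer an internal error; there is none. This stands.
- **Requiring growth and WCC together does not make WCC alone sufficient.** A low-growth sample fails the confirming rule whatever its WCC, and the laboratory procedure that might settle the matter is not shown. This stands as logic. But the proposal does not need raised WCC to prove UTI, only to make its absence less certain. Ambiguous episodes with intermediate growth, or with high growth and low WCC, are already kept out of both the confirmed and the unsupported groups. The same reasoning favours separating low growth with raised WCC.
- **The protocol does not say that a raised IRR in this group will be taken as misattribution.** Correct. A clear gradient from the confirmed to the unsupported group would in itself favour the primary hypothesis. Estimates for the prerisk period and for four windows to day 90 also help, since a late excess is hard to explain by misread early symptoms. An early excess stays ambiguous.
- **The widened sensitivity analysis moves both cut-offs at once.** A reader might infer that it cannot be interpreted. The article plans it only to explore a wider definition, and it serves that purpose. It cannot show which cut-off caused a change, but the article does not promise that.
- **A condensed article may leave stratification to an analysis plan.** A split by WCC could indeed sit there. The cut-offs and the stated purpose of this group are nevertheless fixed in the article, and the comment is on those.

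**Conclusion.** The point holds as a limit on interpretation. Secondary analysis 3 uses growth alone to define a group whose purpose is to detect misattributed symptoms, although the plan's confirming rule also relies on WCC. A raised IRR in that group therefore has two readings that pull in opposite directions.

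The size cannot be established from the document, which does not give the share with raised WCC. Over assumed shares of 10% to 30%, the apparent IRR without any misattribution is 1.03 to 1.09 if the true IRR is 1.3, and 1.1 to 1.3 if it is 2.0. Both effect sizes are assumptions about the truth, and the calculation gives every raised-WCC episode the full effect.

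A reader might go further and conclude that secondary analysis 3 is unusable. The document does not support that: the group is consistently defined, and the blurring is proportional to an unknown share. Nor does it show that intermediate episodes are lost. They enter the widened sensitivity analysis and may enter secondary analysis 2.

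**What to change.** Keep secondary analysis 3 as planned. In Table 2 and the accompanying Exposure text, add that it will also be reported in two parts:

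- growth <1x10^7 CFU/L with WCC <1x10^8/L, named in advance as the group used to judge misattribution;
- growth <1x10^7 CFU/L with WCC ≥1x10^8/L, shown separately, with its number of episodes so that the share is known.

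Optionally, run the widened-definition sensitivity analysis one cut-off at a time beside the joint version: growth ≥1x10^7 CFU/L with the WCC criterion kept, and growth ≥1x10^8 CFU/L with the WCC criterion dropped. The joint version stays as the overall robustness check.

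No new type of data is needed, since the primary definition already uses WCC. The cost is some wording, a few extra model runs, and wider intervals in the two parts than in the whole group.

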We will use the SAIL Databank to access the following linked data: Welsh Longitudinal General Practice data (WLGP), Patient Episode Database for Wales (PEDW), Welsh Results Reporting Service (WRRS). The WLGP contains data from 84% of general practices in Wales, consisting of longitudinal data for 2.6 million Welsh residents, representing 84% of the population.^24^ Demographic data, clinical diagnoses and prescription data are included. The PEDW contains International Classification of Disease version 10 (ICD-10) coded diagnoses for admissions to any Welsh hospital.^25^ The WRRS contains data on all tests requested from primary and secondary care National Health Service (NHS) Wales organisations processed and analysed in NHS Wales laboratories, including requests for urine microscopy, culture and antibiotic susceptibilities.^26^ Data are available from the data sources at varying times based on when clinical information systems began, with data quality improving over time. As such, for our study, based on our approvals and where the data sources have consistent coverage and quality, we will be using them between 1 January 2010 and 31 December 2020.

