### Study design

Individuals who experience UTIs and individuals who do not can differ in unmeasured ways and hence could be sources of residual confounding. We will use the SCCS design method to deal with this issue. The SCCS method is an epidemiological study design for which individuals act as their own control so that both measured and unmeasured characteristics that vary between individuals are completely controlled.^27^ Only individuals who have experienced an outcome and exposure of interest are included. The SCCS method compares the incidence of an outcome during predefined risk periods with incidence during baseline periods (all times outside of risk and prerisk periods) and estimates the temporal association between a transient exposure and outcome. Time-invariant covariates (eg, sex) are inherently controlled for, and time varying covariates (eg, age) are adjusted for within the models. The method was originally developed to investigate associations between vaccinations and acute adverse events, such as aseptic meningitis,^28 29^ but has since been applied in a range of epidemiological settings,^30–32^ including non-acute events such as autism.^33^ As with other study designs, the SCCS method makes several assumptions that need to be met in order to obtain valid and unbiased estimates, but there are model extensions which provide solutions to violations of these assumptions under certain circumstances.^34^ The model assumptions, how they apply to our study, and the solutions to violations of the assumptions are given in table 1.

**Table 1 T1:** Model assumptions and solutions to violations of those assumptions

Assumption	How the assumption applies to this study	Solution	Example of use of the solution in the literature
Subsequent exposures should not be affected by previous events.	We might see a temporary increase in UTIs subsequent to an MI or stroke event, which would bias estimates towards the null.	Apply a prerisk period.	Gibson *et al* studied the association between prescription drugs and road traffic accidents. As some drugs may be used to treat anxiety or pain caused by the crash, a 4-week pre-exposure period was included.^37^

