	As both MI and stroke have relatively high death rates, the length of the observation period is dependent on events, and no further exposures are possible after death.	Use an event-dependent observation period model extension^38^ and conduct a sensitivity analysis that repeats the analysis, excluding individuals who died within 30 days of the event.	Bruer *et al* used the event-dependent observation period model extension in their study on the association between antipsychotic drugs and myocardial infarction.^39^ Langan *et al* studied the risk of stroke following herpes zoster. They conducted a sensitivity analysis excluding individuals who died within 90 days of stroke.^40^
Event rates are constant within defined periods	MI and stroke are more common in older individuals and may be affected by seasonal changes.	Control for age and season effects.	Grave *et al* studied the association between seasonal influenza vaccination and Guillain-Barré syndrome. They adjusted for calendar month, as the vaccinations are seasonal by design.^41^ In a study of the association between chickenpox and stroke, Thomas *et al* adjusted for age in 5-year age bands.^42^
Events are independently recurrent or rare.	MI and stroke are not independent: once an individual has a first event, they are more likely to have a second.	Study first events only.	Langan *et al* began the observation period 12 months into follow-up time to ensure first stroke events had been correctly identified.^40^

MI, myocardial infarction; UTIs, urinary tract infections.

A diagrammatic representation of observation time for an individual in the proposed SCCS design is given in figure 1. Risk periods start on the date of an UTI and end 90 days later. The date of an UTI is the earliest date of occurrence of any of the events necessary for each different UTI definition. For example, the definition of UTI in our primary analysis is a combination of an UTI-related diagnostic code and antibiotic prescription in WLGP data and a urine culture result that supports a diagnosis of UTI in the WRRS data, occurring within a 7-day window. In this case, the date of the UTI would be the date of whichever of the following events occurred first: UTI-related diagnostic code, antibiotic prescription, supporting urine culture.

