### Outcomes

Outcomes of interest are acute MI or stroke, as identified by ICD-10 codes from inpatient diagnoses recorded in the PEDW. A list of ICD-10 codes to be used are given in online supplemental material A.

10.1136/bmjopen-2022-064586.supp1Supplementary data

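### In secondary analyses 4 and 5, dating a hospital UTI at its earliest component can place an MI or stroke on day 0 of the risk period when the UTI was sampled after it in the same admission

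*Protocol article*

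**What the plan says.** The outcome (Outcomes section): "Outcomes of interest are acute MI or stroke, as identified by ICD-10 codes from inpatient diagnoses recorded in the PEDW".

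The hospital exposure (Exposure section): "Secondary analysis 4 will focus on individuals with a hospital admission with an UTI-related ICD-10 code and a microbiology record of a urine sample". Table 2 sets the timing for analysis 4: "Two codes occur within a 7-day window". It does not fix which of the two comes first. The hospital route carries over to the next analysis: "Secondary analysis 5 combines the primary analysis, and secondary analysis 4".

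The database (Data section): "The PEDW contains International Classification of Disease version 10 (ICD-10) coded diagnoses for admissions to any Welsh hospital". No date for an individual diagnosis is described.

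The dating rule (Study design, repeated in the title of Table 2): "The date of an UTI is the earliest date of occurrence of any of the events necessary for each different UTI definition".

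The risk period runs from day 0 to day 90 (Exposure), after a 7-day prerisk period. The Statistical analysis section lists reported bands of 1–7, 8–14, 15–28 and 29–90 days.

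Table 1 foresees infection after the event: "We might see a temporary increase in UTIs subsequent to an MI or stroke event". It expects bias towards the null and answers with the prerisk period.

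**The concern.** In analyses 4 and 5 one hospital admission can supply both the outcome and one of the two components of the exposure. UTI is a plausible complication of a stroke or MI admission, as Table 1 accepts. Nothing in the article excludes a UTI coded in the same admission as the event, or requires the urine sample to come before the event.

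The prerisk period protects against post-event UTIs only if the UTI is dated after the event. The earliest-component rule can remove that gap by moving the UTI date back to the admission date. Infections caused by the event would then count as exposure at the time of the event, which favours the study hypothesis.

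What is at stake is one named comparison in Objective 2, the UTI diagnosed and treated in hospital. A raised IRR there could be read as a real effect of hospital UTI.

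**Working it through.** **1. The plan's design figure, used below as a yardstick.** Sample size and power states 90% power for an IRR of 1.3 at alpha 0.05, with 10% exposed and a 90-day window. Ten per cent of 51,656 MI and 58,146 stroke cases is about 5,166 and 5,815 exposed cases.

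I used the signed-root likelihood-ratio formula for the self-controlled case series without age effects, two-sided alpha assumed:
- n = (z_α + z_β√B)² / A
- A = 2[p ln ρ − ln(ρr + 1 − r)], with p = ρr/(ρr + 1 − r)
- B = (ln ρ)²/A × ρr(1 − r)/(ρr + 1 − r)²
- ρ = 1.3, r = 90/T, and T the mean observation length under Summary of cases

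| Outcome | T (days) | Power |
|---|---|---|
| MI, men | 3251 | 0.911 |
| MI, women | 2981 | 0.931 |
| Stroke, men | 2981 | 0.954 |
| Stroke, women | 2796 | 0.964 |

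The stated figure is reproduced. The point below does not depend on it.

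**2. Tracing the dates.** Take a stroke admission on day 0, a positive culture on day 4 and a UTI code on the same admission. Assume the PEDW code carries the admission date.
- Code and culture are 4 days apart, so the 7-day window is met.
- Earliest component: the UTI is dated day 0, and the stroke falls on day 0 of the risk period.
- Sample date instead: the UTI is dated day 4, and the stroke falls 4 days before it, inside the 7-day prerisk period.

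The stated rule therefore defeats the plan's own safeguard in this sequence. Lengthening the prerisk period to 14 days, listed as a sensitivity analysis of the primary result, cannot move an event off day 0.

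**3. Illustrative size.** Let the true IRR be 1. Let q be the share of included cases that are same-admission pairs placed on day 0, and r = 91/T (days 0 to 90). The other cases' events are spread evenly over observation time, with one risk period each and no age or season effect. Then

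IRR(0–90) = [(q + (1 − q)r)/r] / (1 − q) = 1 + q/[(1 − q)r].

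With r = 91/2796 = 0.0325 and r = 91/3251 = 0.0280:

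| q (assumed) | T = 2796 | T = 3251 |
|---|---|---|
| 0.5% | 1.15 | 1.18 |
| 1% | 1.31 | 1.36 |
| 2% | 1.63 | 1.73 |
| 5% | 2.62 | 2.88 |
| 10% | 4.41 | 4.97 |

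Setting the IRR to 1.3 gives q/(1 − q) = 0.3r, so q = 0.97% (T = 2796) or 0.83% (T = 3251). A share of about 1% is enough to produce the design IRR with no effect present.

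If day 0 were joined to days 1–7 only, r becomes 8/T and q = 1% gives 4.53 to 5.10.

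**4. If day 0 is in no band.** The pairs then leave the numerator. The rates in days 1–90 and in baseline both shrink by the factor (1 − q), and the IRR stays at 1. The bias therefore depends on how day 0 is handled.

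**The case against.** **PEDW dating is not stated.** This stands. Admission dating is an assumption, made plausible by the Data section's description of codes attached to admissions. With consultant-episode dates, a UTI coded in a later episode would be dated after the event and could fall in the prerisk period, so the problem shrinks to same-episode pairs. An article may also leave such detail to a fuller document. The earliest-component rule, however, is stated, and stated for every definition.

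**The result is a tie.** A reader might infer that the UTI is recorded as strictly preceding the event. Under admission dating it is not: both fall on the same day. The reported bands begin at day 1 and may leave that day out, in which case step 4 applies. But the Exposure section and the primary hypothesis both count from day 0, and the article does not say that day 0 is set aside.

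**Table 1 already deals with post-event UTIs.** It does so only when the UTI is dated after the event. Its stated direction, towards the null, does not hold for these pairs.

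**Removing same-spell pairs brings its own bias.** This also stands. Such a rule makes exposure depend on whether the outcome occurred in the same stay. It would drop patients admitted with a UTI who then have an event, in the early days where the Introduction reports the highest risk. It belongs in a sensitivity analysis.

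**Conclusion.** The point holds for secondary analyses 4 and 5 and should be fixed. Under admission (or same-episode) dating of PEDW codes, and with day 0 counted in the risk period, the earliest-component rule turns some post-event UTIs into exposure on the event day and biases the IRR upwards.

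The actual size cannot be given, because the documents contain no same-admission share for either outcome. The illustration runs from about 1.3–1.4 at 1% of included cases to 4.4–5.0 at 10%. These are shares of the cases included in the analysis, not of all MI or stroke admissions. The observation lengths are means over all cases, and the 10% exposure assumed for power is not a figure for hospital UTI.

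Two stronger readings are not supported. One is that the study's main result is compromised: the primary analysis and secondary analyses 1–3 take exposure from GP codes and prescriptions, without a PEDW code, so Objectives 1 and 3 are untouched. The other is that a large bias has been shown: the documents establish that the path is open, not how often it is taken.

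**What to change.** 1. In analyses 4 and 5, date hospital UTIs by urine-sample date instead of earliest component, and state which date a PEDW code carries.
2. Reconcile the risk period that starts at day 0 with the reported bands that start at day 1, by analysing day 0 as its own stratum. This also isolates the same-day ties that sample dating leaves.
3. Report the number of UTI and event pairs coded in the same hospital spell, for MI and stroke separately.
4. Repeat analyses 4 and 5 without those pairs, as a sensitivity analysis.

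The cost is a little more analysis work and a few sentences of text. The sensitivity analysis will lose some true UTI-then-event sequences within one admission and may be biased towards the null, which should be said when it is reported. Where a patient is admitted with a UTI but sampled later, sample dating also moves an event dated before the sample from the risk period into the prerisk period, whose IRR the plan already reports.
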